## Abstract

**Background:**

Traumatic experiences and, more specifically, posttraumatic stress disorder (PTSD) are highly prevalent among substance use disorder (SUD) patients. This comorbidity is associated with worse treatment outcomes in substance use treatment programs and more crisis interventions. International guidelines advise an integrated approach to the treatment of trauma related problems and SUD. Seeking Safety is an integrated treatment program that was developed in the United States. The aim of the current study is to test the efficacy of this program in the Netherlands in an outpatient SUD population.

**Methods/Design:**

A randomized controlled trial (RCT) will be used to test the efficacy of Seeking Safety compared to Cognitive Behavioral Therapy (CBT) in a population of SUD outpatients. Each treatment will consist of 12 group sessions. The primary outcome measure will be substance use severity. Secondary outcome measures are PTSD and trauma symptoms, coping skills, functioning, and cognitions. Questionnaires will be administered at the start of treatment, at the end of treatment (three months after the start of treatment) and at follow-up (six months after the start of treatment).

**Discussion:**

This study protocol presents a RCT in which the efficacy of an integrated treatment for comorbid PTSD and SUD, Seeking Safety, is evaluated in a SUD outpatient population compared to CBT. It is expected that the intervention group will show significantly more improvement in substance use severity compared to the control group at end-of-treatment and at follow-up. Furthermore, a lower drop-out rate is expected for the intervention group. If the intervention proves to be effective, it can be implemented. A cost-effectiveness analysis will be conducted to evaluate the two treatments.

**Trial registration:**

The protocol for this study is registered with the Netherlands Trial Register with number NTR3084 and approved by the local medical ethical committee (METC\11270.haa).

## Background

A history of traumatic experiences is very common among substance use disorder (SUD) patients, with estimates ranging from 55%–99% [1,2]. Furthermore, high rates of posttraumatic stress disorder (PTSD) have been found among SUD patients. The rate of drug and/or alcohol dependence in veteran populations varies from 40% to 75% [3,4]. In civilian populations with lifetime PTSD prevalence of SUD’s ranges from 22% to 43%, compared with 2% to 15% in persons without PTSD [5]. Among SUD patients the rate of PTSD varies between 11%–60% for current PTSD and 33%–75% for lifetime PTSD [2,6,7].

These high rates of comorbidity suggest that PTSD and SUD are functionally related. Several pathways have been described in which these two disorders relate to one another, such as the “self-medication hypothesis” in which PTSD precedes SUD [8]. When SUD precedes PTSD, a likely explanation is that substance users often risk hazardous situations to sustain their habit, and therefore experience high levels of physical and psychological trauma. This in turn, increases the chance of developing a PTSD [9]. Finally, there is accumulating evidence that both disorders share neurobiological systems, so that continued substance use may increase an individual’s susceptibility to developing PTSD following a trauma and, vice versa, that PTSD increases the vulnerability for developing SUD [10].

The association between SUD and PTSD is clinically significant, as well as the association with traumatic experiences in general, because trauma exposure and related PTSD symptoms have the potential to affect SUD treatment. These symptoms include re-experiencing the trauma, avoidance, and increased anxiety or hyperarousal. In addition to related symptoms of depression, they interfere with patients’ abilities to adhere to and benefit from substance abuse treatment [11,12]. International guidelines advise to integrate the treatment of SUD and trauma related disorders such as PTSD [13-15].

Seeking Safety is a therapy that was developed in the United States as an integrated treatment for PTSD and SUD [16]. It has also been found a feasible treatment for patients who are subthreshold on these disorders or who have just one or just the other disorder. The treatment is cognitive-behavioral, as well as addressing interpersonal and case management domains. It is present-focused and designed to help patients learn coping skills to attain safety from trauma/PTSD and substance abuse. Seeking Safety has had over 20 published studies (see [17], for a comprehensive review). It has shown to reduce substance use and PTSD symptom severity in comparison with a control group in female patients [18], female adolescents [19], incarcerated women with SUD and PTSD [20] and in veterans in outpatient treatment [21], for example. Various quasi-experimental and non-controlled studies show positive outcomes for Seeking Safety [22-31]. The treatment has shown positive results in the United States and is the only model for PTSD/SUD thus far to impact both PTSD and SUD [17]. The French translation of Seeking Safety has had positive findings and satisfaction in a Canadian study [32]. The Dutch translation, however, has never been studied. Cultural differences in expectancies from health care providers, differences in communicating and general views may cause differences in adherence and efficacy.

### Aims

The aim of this study is to test the efficacy of Seeking Safety versus standard CBT in a Dutch sample of outpatient SUD patients who have experienced at least one traumatic event. As the population under study consists of patients in treatment for substance use, the primary outcome measure is substance use severity. Secondary outcome measures are PTSD and trauma symptoms, coping skills, functioning, and cognitions. We will also assess drop-out and satisfaction.

A second aim of the study is to perform a cost-effectiveness analysis to compare the two treatments.

## Methods

### Study design

For this study a randomized controlled design is used. Semi-structured interviews and self-report questionnaires will be used to measure change over time on variables at three time points: at the start of the treatment (t = 0), at end of the treatment (t = 1) and three months after the end of treatment (follow-up, t = 2). These points in time are chosen to conform to standard evaluation procedures within our facility. Routine outcome monitoring is conducted at completion of treatment for the outpatients or at three months after the start of treatment. The administration of questionnaires for the study will be synchronized with this monitoring. Both Seeking Safety and CBT will consist of weekly group sessions of 1 3/4 hours for 12 weeks (12 sessions total). This design keeps dosage equivalent across the treatment conditions, and has been used successfully in a prior recent RCT of Seeking Safety [21]. Both Seeking Safety and CBT will be offered in closed-group format, as this is the standard in the control condition. Participants will not be financially rewarded for their participation. The results of the study will be presented following the CONSORT guidelines [33].

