### Sample size calculation

The sample size for this study is calculated using a significance level of 95% (p < 0.05), a power of 80% and the same number of patients in the intervention and control group (ratio = 1).

Primary outcome variable is substance use severity as measured with the EuropASI. In recent studies, conducted within the same institution [34] but with a population of inpatients, a mean baseline score of 5.2 was found for the alcohol domain and 4.0 for the drugs domain. We expect the mean baseline scores for the outpatients to be somewhat lower, however not considerably. For comparison of baseline scores on the EuropASI, see [22,23]. For practical reasons we are using the mean of both domains (alcohol and drugs) for the sample size calculation. Thus, the mean score for substance use severity will be somewhat lower than (5.2 + 4.0)/2 = 4.6 with a standard deviation of 2.7. For this sample size calculation we will use a baseline score of 4.0 with the same standard deviation. We expect the substance use severity to improve with 60% [23] to 1.6 (SD = 2.0) at end-of-treatment for the intervention group and 2.8 (SD = 2.0) for the control group. We used PS – Power and Sample Size Calculation to calculate the sample size, which resulted in a sample size of 45 patients in each group. Drop-out rates for this treatment are available for the past years from a management information system and are estimated around 20%. This drop-out rate may seem low compared to the numbers that are known from previous studies in SUD patients. However, we will use this percentage to calculate the number of patients that are needed, but will perform an analysis on drop-out halfway through the study. When the drop-out rates turn out to be higher than expected, an amendment will be proposed to the medical ethical committee to continue including patients for an extended period of time. Because of the calculated drop-out rate, an extra 9 participants will be included in both the intervention and the control group, yielding a total of 108 participants for the randomized controlled trial. Based on treatment entry numbers from previous years, approximately two years will be needed to include all patients. Furthermore, this number of patients seems plausible considering sample sizes in previous studies that show similarity in design [21,22].

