### Treatment program

#### Intervention

Patients will be randomized to either Seeking Safety or to standard CBT. Seeking Safety was originally designed as an integrated model for patients that have both PTSD or trauma-related symptoms and SUD. The treatment manual has recently been translated into Dutch [35]. Seeking Safety consists of 25 structured topics, which can be conducted in group or individual modality. In this study, it will be conducted in group modality. Topics are evenly divided among cognitive, behavioral and interpersonal coping skills, with a goal of helping patients attain safety in their lives. ‘Safety’ is defined as reduction in substance use and destructive behavior, establishment of a network of supportive people and self-protection from dangers associated with the disorders.

There will be one Seeking Safety topic per session for the duration of three months, making it possible for patients to receive 12 topics. The topics to be used are: Safety; PTSD-Taking Back Your Power; When Substances Control You; Grounding; Healing from Anger; Honesty; Taking Good Care of Yourself; Compassion; Red and Green Flags; Asking for Help; Creating Meaning; and Life Choices.

Patients that attend a minimum of 7 sessions will be considered “minimum dose completers” [36]. Every session is conducted according to a fixed structure, starting with a check-in to find out how each patient is doing and both strengths and problems in coping since the last session. Second, a quotation is discussed followed by a discussion of the hand-outs in which the topic of the session is related to the patients’ life. This is also the place where coping skills are shared and discussed. Each session ends with a check-out where patients are encouraged to share one thing they have learned during the session and to formulate a commitment (homework) for the next session. The sessions will be facilitated by one therapist or social worker. The therapists and social workers all received a two-day training in Seeking Safety. Furthermore, all sessions will be videotaped and a random sample of 20% will be selected for review. Thus, quality and adherence will be monitored and ongoing supervision will be provided.

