### Statistical analyses

All analyses will be executed using SPPS for Windows version 18.0. Frequency tables will be provided for all baseline, end of treatment and follow-up variables. Descriptive statistics will include mean, median, interquartile range, numbers and percentages of patients, as appropriate. If applicable, 95% confidence intervals will be given. To compare differences between groups (Seeking Safety vs CBT) *t*-test or mann whitney U tests will be used in case of continuous variables, as appropriate. For categorical variables chi-squared tests will be used. Repeated measures analyses (mixed models in SPSS) will be used to test the differences between the treatment conditions over time in severity of substance use problems as measured by the EuropASI severity score (pre, post and follow-up). The data will be tested for normality and transformed as appropriate when the data are skewed. Analyses will be based on the intent-to-treat principle. Participants have to attend at least one session to be considered part of this group. Differences regarding gender will be analysed and when appropriate, gender will be included in the analyses as a confounder or effect modifier. Multiple Imputation will be used for missing data. Effect sizes will be calculated to facilitate comparison of improvement between the two groups. Linear regression analyses will be used to determine the predictors of change in substance use and trauma symptoms. Also, amount of prior psychiatric treatment will be used in the analysis as a covariate.

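### Both arms are treated in closed therapy groups, but the sample size assumes independent patients and no planned test names a therapy-group term

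*Protocol article*

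**What the plan says.** Randomization is at patient level (Randomization section). Treatment is not individual: "Both Seeking Safety and CBT will be offered in closed-group format, as this is the standard in the control condition". Each arm has weekly sessions for 12 weeks, and the Comparison condition section repeats the closed format for CBT. For Seeking Safety, the Intervention section adds: "The sessions will be facilitated by one therapist or social worker". No staffing figure is given for CBT.

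The Sample size calculation sets out its whole derivation. It uses "a significance level of 95% (p < 0.05), a power of 80" per cent, equal arms, and expected improvement "to 1.6 (SD = 2.0) at end-of-treatment for the intervention group and 2.8 (SD = 2.0) for the control group", "which resulted in a sample size of 45 patients in each group". Nine more per arm for drop-out brings the total to 108. No group size, ICC or design effect appears.

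Statistical analyses lists t-tests or Mann-Whitney U tests, chi-squared tests and linear regression. For the EuropASI it says: "Repeated measures analyses (mixed models in SPSS) will be used to test the differences between the treatment conditions over time", with pre, post and follow-up as the time points. Gender and prior psychiatric treatment are named as possible model terms. Therapy group and therapist are not.

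**The concern.** Randomising patients individually makes them independent at baseline. It does not keep them independent once they share three months of sessions, and the primary outcome is measured at the end of those sessions. Members of a closed group share peers, discussion and timing and, at least in Seeking Safety sessions, a sole facilitator. If this makes their outcomes alike, the arm means vary more than an independent-patient formula allows.

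Two things are then at stake. A test that ignores the groups gives confidence intervals that are too narrow and rejects too often, so a few unusually good groups could pass for a treatment effect. And a sample size built on independence promises more power than a valid test would have. The article intends the result to inform policy makers and possibly broad implementation, so a false positive would matter.

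**Working it through.** **Step 1: reproduce the stated 45.** Inputs from Sample size calculation: difference 2.8 - 1.6 = 1.2; SD 2.0; standardised difference 1.2/2.0 = 0.6; alpha 0.05, taken as two-sided; power 80%; ratio 1.

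- Normal approximation: n = 2 x (1.960 + 0.842)^2 x 2.0^2 / 1.2^2 = 43.6, so 44 per arm.
- t-test: 44.6, so 45 per arm, with 80.4% power at 45.
- One-sided: 35 per arm, which does not fit.

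The stated figure is therefore the independent-patient t-test, that is, a design effect of exactly 1.

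**Step 2: the margin.** The design effect is DE = 1 + (m - 1) x ICC, where m is the number of trial patients per group. Power stays at 80% only while 45/DE is at least 44.6, so DE can be at most 45/44.6 = 1.009. With m = 6 that is an ICC of about 0.009/5 = 0.002.

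**Step 3: effect of clustering.** Neither m nor the ICC is in the article; both are assumed. Power is for a test that allows for clustering, with 45 analysed per arm and SD 2.0 x sqrt(DE), on the t distribution with 88 df. The type I error of the unadjusted test is 2 x [1 - Phi(1.96/sqrt(DE))].

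| m | ICC | DE | 45/DE | Power | Type I error, unadjusted |
|---|---|---|---|---|---|
| 3 | 0.01 | 1.02 | 44.1 | 80% | 5.2% |
| 3 | 0.05 | 1.10 | 40.9 | 77% | 6.2% |
| 3 | 0.10 | 1.20 | 37.5 | 73% | 7.4% |
| 6 | 0.01 | 1.05 | 42.9 | 78% | 5.6% |
| 6 | 0.05 | 1.25 | 36.0 | 71% | 8.0% |
| 6 | 0.10 | 1.50 | 30.0 | 63% | 11.0% |
| 10 | 0.01 | 1.09 | 41.3 | 77% | 6.0% |
| 10 | 0.05 | 1.45 | 31.0 | 65% | 10.4% |
| 10 | 0.10 | 1.90 | 23.7 | 53% | 15.5% |

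**Step 4: is about 6 per group reasonable?** The article expects 108 patients in about two years. If one new group started per arm per quarter (an assumption), there would be 8 x 2 = 16 groups, 108/16 = 6.75 randomised per group and 6.75 x 45/54 = 5.6 analysed. If routine patients outside the trial also sit in the groups, m is smaller, which is why the table starts at 3.

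**Step 5: two further influences.**

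- Few groups: 90 analysed patients in groups of 6 make 15 groups and 13 group-level df. At ICC 0.05 power falls from 71% to about 65%.
- Baseline adjustment: the sample size takes no credit for it. With an assumed pre-post correlation r, the variance is multiplied by (1 - r^2). At m = 6 and ICC 0.05, r = 0.4 gives 1.25 x 0.84 = 1.05 and power of about 78%; r = 0.5 gives 1.25 x 0.75 = 0.94 and about 83%. Both figures use 88 df and let baseline explain the group component as fully as the patient component. That is generous, because group effects arise after baseline.

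**The case against.** The strongest reply is that this is a condensed article. Random-effects structure and degrees-of-freedom methods commonly sit in an analysis plan, and a mixed model is already named that could carry a group term. That stands in part: one cannot conclude that the analysis will ignore groups, only that the article describes the model solely as repeated measures over time and names other terms but not this one. It does not rescue the sample size, whose calculation is shown in full and reproduces only with no clustering.

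Second, the size of the problem is assumed. This stands. At ICC 0.01 power is about 77% to 80% and the type I error is at most about 6%, which is minor. Baseline adjustment could recover part of the power. It would not correct a standard error that omits a positive group component.

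Third, a reader might infer that one therapist leads every group in both arms. The article does not say so. The single facilitator appears only under the Seeking Safety intervention, and even there the text does not say that the same person leads a group throughout. The argument rests on the closed groups, which are documented for both arms.

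**Conclusion.** The point holds conditionally and should be fixed. The sample size assumes independent patients while both arms are treated in closed groups, and no planned test names the group. For any positive within-group correlation, the standard errors of tests without a group term are too small. The 80% power is then missed under the calculation's own assumptions, beyond a margin of about 0.4 of a percentage point.

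How much this matters depends on two figures the article does not give. Over 3 to 10 trial patients per group and ICC 0.01 to 0.10, the design effect is 1.02 to 1.90, power is about 80% down to 53%, and unadjusted type I error is about 5.2% to 15.5%. The middle case (6 per group, ICC 0.05) gives about 71% and 8%. Few group-level degrees of freedom would lower power further; baseline adjustment could offset part of the loss.

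It is tempting to state flatly that the trial's real power is below 80%. The documents do not support that: the ICC could be close to zero, and the gain from baseline is unknown.

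**What to change.** - Record therapy-group and therapist identifiers prospectively for every patient in both arms; they may not be recoverable later.
- Add a random intercept for therapy group to the primary mixed model, with Satterthwaite degrees of freedom. Since groups form after baseline, let this effect act on the post-baseline measurements. If baseline is one of the modelled outcomes, an intercept constant over all three times would largely cancel from the treatment-by-time contrast and leave its standard error uncorrected.
- Use the same model for the other continuous outcomes in place of t-tests.
- In Sample size calculation, state the assumed group size and ICC, give the design effect, and restate the power for 108 patients.

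The cost is two recorded variables and one model term. Confidence intervals will be somewhat wider and the stated power lower, and with few groups the group variance will be estimated imprecisely. The change itself requires no extra patients, but it does not restore lost power.

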### Participants

#### Recruitment

All patients that enter group-based weekly therapy are asked to participate during intake. They will receive a letter explaining the purpose of the study, what they can expect and the requirements to participate, and an informed consent. They are asked to read the information carefully and decide on participating within two days.

#### Inclusion criteria

Eligible participants for this study are both male and female patients that enter group-based outpatient substance use treatment. They have to be 18 years of age or older and sufficiently fluent in the Dutch language. In this study we will include all patients who have experienced a traumatic event and have trauma-related symptoms. These are assessed by asking the patients whether or not they have experienced a traumatic event, and have a score of at least 40 on the Self-report Inventory for PTSD (SRIP). Furthermore, patients meet current DSM-IV criteria for substance dependence or abuse and have active substance use in the previous 30 days.

#### Exclusion criteria

Patients will be excluded at intake if they have current uncontrolled psychotic or severe bipolar disorder; or serious danger to self or others (defined as stated intent to commit suicide or an act of violence, with clear intent and plan). These will be determined by a psychologist or a psychiatrist.

#### Randomization

Randomization will be at patient level. The participants will be randomly appointed to either the control group or the experimental group. The care-takers are blind for this randomization. Envelopes will be distributed to the treatment facility and these contain the questionnaires that will be administered at t = 0. After completing the questionnaires patients will be randomized based on a predefined randomization schedule. Randomization will be performed in blocks of 4 and 8 (in random order). The research assistants that administer the questionnaires for t = 1 and t = 2 will be kept blind for this randomization.

### Sample size calculation

The sample size for this study is calculated using a significance level of 95% (p < 0.05), a power of 80% and the same number of patients in the intervention and control group (ratio = 1).

Primary outcome variable is substance use severity as measured with the EuropASI. In recent studies, conducted within the same institution [34] but with a population of inpatients, a mean baseline score of 5.2 was found for the alcohol domain and 4.0 for the drugs domain. We expect the mean baseline scores for the outpatients to be somewhat lower, however not considerably. For comparison of baseline scores on the EuropASI, see [22,23]. For practical reasons we are using the mean of both domains (alcohol and drugs) for the sample size calculation. Thus, the mean score for substance use severity will be somewhat lower than (5.2 + 4.0)/2 = 4.6 with a standard deviation of 2.7. For this sample size calculation we will use a baseline score of 4.0 with the same standard deviation. We expect the substance use severity to improve with 60% [23] to 1.6 (SD = 2.0) at end-of-treatment for the intervention group and 2.8 (SD = 2.0) for the control group. We used PS – Power and Sample Size Calculation to calculate the sample size, which resulted in a sample size of 45 patients in each group. Drop-out rates for this treatment are available for the past years from a management information system and are estimated around 20%. This drop-out rate may seem low compared to the numbers that are known from previous studies in SUD patients. However, we will use this percentage to calculate the number of patients that are needed, but will perform an analysis on drop-out halfway through the study. When the drop-out rates turn out to be higher than expected, an amendment will be proposed to the medical ethical committee to continue including patients for an extended period of time. Because of the calculated drop-out rate, an extra 9 participants will be included in both the intervention and the control group, yielding a total of 108 participants for the randomized controlled trial. Based on treatment entry numbers from previous years, approximately two years will be needed to include all patients. Furthermore, this number of patients seems plausible considering sample sizes in previous studies that show similarity in design [21,22].

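### The 20% drop-out allowance is added to the 45 patients required instead of being taken from those randomised, so 108 randomised patients leave about 43 per arm and power slightly below 80% (minor)

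*Protocol article*

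**What the plan says.** Everything needed is in one section of the protocol article, Sample size calculation.

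- The design values are "a significance level of 95% (p < 0.05), a power of 80" per cent, with equal allocation.
- The expected substance use severity falls from a baseline of 4.0 "to 1.6 (SD = 2.0) at end-of-treatment for the intervention group and 2.8 (SD = 2.0) for the control group".
- The calculation is reported as one "which resulted in a sample size of 45 patients in each group".
- Drop-out rates from the institution's management information system "are estimated around 20" per cent. The article grants that this may look low for this population, but says "we will use this percentage to calculate the number of patients that are needed".
- The result is that "an extra 9 participants will be included in both the intervention and the control group, yielding a total of 108 participants".

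The section also plans a look at drop-out halfway through the study. If drop-out is higher than expected, an amendment to extend inclusion would be proposed. No numerical threshold is given.

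**The concern.** A drop-out rate is a fraction of the patients who enter. To have a given number left, the required number is divided by the fraction retained. The article takes 20% of the number required and adds it. The two methods differ, and the additive one always falls short.

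At stake is whether the planned 108 delivers what the section claims for it: 45 patients per arm and 80% power at the drop-out rate the section itself adopts. The halfway look would not repair a shortfall at that rate, because it responds only to drop-out above expectation.

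**Working it through.** "Completer" below would be ambiguous, because the article uses a similar term for patients who attend at least 7 sessions. Here it means only a patient who has not dropped out.

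**Inputs (all from Sample size calculation).** Means 1.6 and 2.8, so the difference is 1.2. SD 2.0 in each arm. Significance level 0.05, power 0.80, ratio 1:1. Required number 45 per arm. Drop-out 20%. Sidedness is not stated.

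**Step 1: reproduce the 45.**
- Normal approximation, two-sided: n = 2 x [SD x (z for 0.975 + z for 0.80) / difference]² = 2 x [2.0 x (1.960 + 0.842) / 1.2]² = 43.6, rounded up to 44.
- Two-sample t-test, two-sided: 44.59, rounded up to 45. This matches the article.
- A one-sided test gives 35 to 36, which does not match. The two-sided test is therefore inferred.

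**Step 2: reproduce the 108.** 45 x 0.20 = 9; 45 + 9 = 54 per arm; 2 x 54 = 108. This matches the article, so the allowance was taken as a share of the 45.

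**Step 3: apply the 20% to those randomised.**
- Completers per arm: 54 x 0.80 = 43.2.
- Completers in total: 108 x 0.80 = 86.4, against 90 required.
- Drop-out that 54 per arm can absorb while keeping 45: 9/54 = 16.7%.

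**Step 4: consistent inflation.** 45/(1 - 0.20) = 56.25, rounded up to 57 per arm and 114 in total. The shortfall is 114 - 108 = 6 patients, or 6/114 = 5.3%. As a check, 57 x 0.80 = 45.6 per arm.

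**Step 5: power for a difference of 1.2, SD 2.0, two-sided 5%.**

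| Completers per arm | t-test | Normal approximation |
|---|---|---|
| 43 | 78.5% | 79.4% |
| 43.2 | 78.7% | 79.6% |
| 44 | 79.5% | 80.4% |
| 45 | 80.4% | 81.2% |
| 45.6 (57 randomised) | 80.9% | 81.7% |

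At 43 per arm, both methods fall below 80%. Against the stated 80%, the loss is 1.5 points by the t-test and 0.6 points by the normal approximation.

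**The case against.** **The loss is too small to matter.** It amounts to about 2 completers per arm and at most 1.5 points of power. The 20% is itself approximate, and no analysis choice or conclusion depends on it. This stands, and it is why the point is minor. It does not make the printed figures agree with each other.

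**Drop-outs are not discarded.** The article never says that the 45 must be evaluable. The 20% appears to be drop-out from treatment, which need not mean a missing end-of-treatment assessment. The Data collection section has patients in both arms assessed at fixed times, and Statistical analyses plans intent-to-treat, mixed models and multiple imputation. This softens the practical consequence. It does not repair the calculation: the section treats drop-outs as losses to be replaced and claims no gain from those methods. If drop-outs counted in full, no extra 9 would be needed.

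**Stronger readings that a reader might infer.**
- *That the trial is seriously underpowered.* The figures do not support this; power stays within 2 points of 80%.
- *That this deficit combines with losses from group treatment, or from leaving out patients who attend no session.* Those would be separate matters. The article gives no figure from which to size them, and they do not arise from this arithmetic.
- *That the halfway look should act above 16.7%.* The article sets no numerical threshold. If true drop-out is the expected 20%, and assuming 54 patients with known status at that look, more than 9 drop-outs would be seen about 66% of the time (binomial). The standard error of a 20% rate in 54 patients is √(0.20 x 0.80/54) = 5.4 points, so the look cannot tell 16.7% from 20%. Such a threshold would usually prompt an extension when drop-out runs as planned.

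**Conclusion.** The point holds as a minor arithmetic error. At the article's own 20% drop-out, 108 randomised patients leave about 43 completers per arm, not 45, and power is about 78.5% (t-test) or 79.4% (normal approximation), not 80%. The planned number keeps 45 per arm only if drop-out is at most 16.7%. The number consistent with 45 completers at 20% drop-out is 114.

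The counts (43.2, 57, 16.7%) follow from the printed figures alone. The power figures also rest on the planned difference and SD, on a two-sided 5% test (inferred because it reproduces 45), and on counting each drop-out as lost to the primary comparison, as the sample size section does.

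**What to change.** Correct the sentence that gives the 108, in one of two ways.

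1. **Keep 108 and restate what it delivers.** At 20% drop-out, 108 randomised patients give about 43 completers per arm and about 78.5% power (two-sided 5% t-test), and 45 per arm is kept only up to 16.7% drop-out. This costs one sentence and a slightly lower stated power, and needs no extra patients.
2. **Keep 80% power and change the number.** Randomise 57 per arm, 114 in total. This costs 6 more patients. The article expects about two years to recruit 108, so at the same rate the addition is 6/108 x 24 months, or a little over one month.

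Either way, state that the test is two-sided. The halfway look at drop-out needs no change on account of this point.
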